
### Study design and setting

The trial is an open-label, randomised, controlled superiority trial recruiting adults who are undergoing elective primary lower-limb arthroplasty with sedation by propofol infusion by effect-site targeting into two equal-sized parallel arms: PMPS and ACPS. The study will be run as a single-centre study at Nottingham University Hospitals National Health Service (NHS) Trust. The trial will be conducted only in a secondary care setting.

### Trial intervention

Propofol 1% is licensed in the UK for “Sedation for diagnostic and surgical procedures, alone or in combination with local or regional anaesthesia in adults and children > 1 month” [14]. The trial will be using propofol within the terms of this license. Patients randomised to PMPS will receive propofol according to the following algorithm: the effect-site target concentration of propofol will be commenced at 0.5 μg.mL^− 1^ and increased by 0.2 μg.mL^− 1^ (when the patient presses the button) to a maximum of 2.0 μg.mL^− 1^. Following a successful button-induced increase in the effect-site target, further button presses will not increase the target concentration for 2 min (this is termed the *lockout period*). If patients do not press the button for 15 min, the effect-site target will reduce by 0.1 μg.mL^− 1^, and will continue to reduce by 0.1 μg.mL^− 1^ every 15 min to a minimum of 0.5 μg.mL^− 1^ in the absence of a button-press. Patients randomised to ACPS will receive propofol according to the following algorithm: the effect-site concentration will be commenced at a level determined by the supervising clinical anaesthetist and incremented and decremented by them as they see fit. No maximum or baseline levels will be pre-specified. This constitutes standard clinical practice. Both groups will use Schnider effect-site TCI modelling.

### Safety

All pre-existing medication taken by a participant as part of their usual medical care will be permitted. Co-administration of sedatives, hypnotics or analgesics during placement of spinal anaesthesia or during the intra-operative sedation regime at the discretion of the supervising clinical anaesthetist will be recorded. Behavioural disinhibition is a well-recognised side-effect of propofol sedation. This occurs regardless of whether the propofol is delivered by intermittent bolus, fixed rate infusion or target-controlled infusion. It manifests as patient movement (usually of the upper limbs) and/or talking. It does not always respond readily to simple verbal command from the supervising clinician to desist. The standard treatment for this is for the supervising clinical anaesthetist to actively alter the depth of sedation at their discretion by either lightening or deepening the degree of sedation according to clinical circumstances and their professional judgement. In either arm of the trial, if a patient displays disinhibited behaviour that is disruptive to surgery or potentially dangerous for the patient (for example, risking pulling out their intravenous cannula), the supervising clinical anaesthetist will be free to alter the patient’s depth of sedation either by lightening or deepening sedation, using a sedative agent of their discretion. This will be recorded. No medications will be specifically prohibited in this trial.

In order to detect physiological changes that may suggest unsafe sedation, both trial arms will have heart rate, respiratory rate, arterial oxygen saturations, blood pressure and depth of sedation measured and recorded at 5 min intervals throughout the sedation period. Adverse events, adverse device events, serious adverse events and serious adverse device events will be recorded and reported to the relevant bodies (trial Sponsor, device manufacturer, Research Ethics Committee, Medicine and Healthcare products Regulatory Agency).

### Inclusion criteria

The inclusion criteria are as follows:Listed to undergo elective primary hip or knee arthroplasty under spinal anaesthesiaExpressing a pre-operative preference for sedation during surgeryAble to communicate in written and spoken EnglishCapable of giving informed consentAge > 18 years

### Exclusion criteria

Allergy to propofolMale patients with body mass index (BMI) > 42 and female patients with BMI > 37Medical contraindication to spinal anaesthesia (for example local infection at injection site, patient refusal, allergy to local anaesthetic agent, untreated systemic infection or untreated coagulopathy)Expressing pre-operative preference for surgery to be performed awake or under general anaesthesiaInability to use handheld trigger system of the patient-maintained propofol sedation device (PMPSD)Pregnancy or breastfeeding

BMI is included as an exclusion criterion since in the Schnider TCI model, lean body mass (LBM) is calculated using the James formula. This has been shown to estimate LBM satisfactorily in normal-weight and moderately obese patients, but paradoxically in male patients with BMI > 42 and female patients with BMI > 37 [15]. As a safety precaution to prevent inaccurate propofol dosing in these groups we have excluded patients with BMI above these thresholds.

### Enrolment

Patient screening for eligibility and recruitment will be conducted at the Theatre admission lounge, Nottingham City Hospital campus. This site is where our patients are usually treated. Screening will be performed by the supervising clinical anaesthetist during their routine pre-operative patient assessment. The supervising clinical anaesthetist will notify a study investigator of potentially eligible patients. The recruited patient will sign and date the approved version of the informed consent form before any procedures specific to the clinical investigation are performed.

The participant’s research data will be gathered during a single visit to hospital, which forms part of usual clinical care. A telephone consultation between a study investigator and each participant will be performed at post-operative day 7–10.

After enrolment, the participant will be given a group-specific laminated educational leaflet explaining their sedation system. Those allocated to PMPS will receive written instructions on the use of the PMPSD and those allocated to ACPS will receive written explanation on how their supervising clinical anaesthetist will sedate them.

A pre-operative questionnaire will be administered to all participants before they are taken to the anaesthetic room. The following data will be recorded: age, gender, whether hip or knee arthroplasty, surgeon initials, supervising clinical anaesthetist initials, patient weight and height, American Society of Anaesthetist Physical Status Classification, respiratory rate, arterial oxygen saturations, heart rate, blood pressure (systolic, diastolic, mean) and sedation score on the Modified Observer’s Assessment of Alertness/Sedation (mOAA/S) Scale.

### Intervention

The usual clinical care of non-invasive physiological monitoring will be established by the supervising clinical anaesthetist. They will insert an intravenous cannula and spinal anaesthesia will be performed. When satisfied that adequate spinal anaesthesia has been accomplished, they will commence the participant on their allocated sedation regime.

Participants allocated to PMPS will have their sedation infusion commenced at the minimum level of 0.5 μg.mL^− 1^ and will be given the handheld trigger button to press. They will be told *“*Press the button if you want to be more sleepy*”*. Participants allocated to ACPS will be commenced on an effect-site-steered TCI propofol infusion. The supervising clinical anaesthetist will control the effect-site target at their discretion.

Both sedation regimes will commence in the anaesthetic room, prior to the participant moving to theatre. A study investigator will record physiological and sedation outcome measures at 5-min intervals throughout the sedation period.

The sedation regime will be discontinued at the end of surgery when skin clips are applied to the wound. This time will be noted by a study investigator. In the PMPS group the handheld button will be withdrawn from the patient and the TCI infusion stopped. In the ACPS group the TCI infusion will be stopped. If, for any reason, the sedation is discontinued prior to end of surgery, the reason will be noted in a free-text narrative response by a study investigator.

### Post-operative period

Participants will be transferred to the PACU where a study investigator will continue physiological and sedation outcome measures until readiness for discharge from PACU is achieved. The modified Aldrete score will be recorded at 5-min intervals from the time the sedation regime stops until the time at which the participant is scored in excess of 9, indicating readiness for safe discharge from PACU. Once participants are ready for discharge from PACU a study investigator will administer a short, group-specific post-operative questionnaire including questions on psychological variables (e.g. anxiety).

On post-operative day 7–10 (the exact timing depending on the availability and convenience of the participant), a study investigator will contact all patients by telephone to conduct a group-specific post-operative telephone questionnaire (including questions on anxiety since the operation and the sedation experience) and a brief structured interview (in order for us to gain more in-depth data on the experience and perceptions of the sedation experience for patients in the PMPS group). The interview will include qualitative responses in order to allow the participant to provide additional information beyond that covered in the questionnaires.

On completion of the post-operative telephone questionnaire the participant’s enrolment in the trial will cease. A SPIRIT schedule of trial enrolment, intervention and assessment is shown in Fig. 1.

**Fig. 1 Fig1:**
[figure not shown]
SPIRIT: Schedule of enrolment, intervention and assessments. THAL, Theatre admission lounge; PACU, Postoperative care unit; PMPS, patient-maintained propofol sedation; ACPS, anaesthetist-controlled propofol sedation)

### Statistical methods

Propofol consumption (milligrams) will be calculated in participants randomised to the two study groups. Body weight (kilograms) and height (centimetres) recorded at the pre-operative assessment will be used. Length of sedation is defined as the time from when the propofol sedation is commenced by the supervising clinical anaesthetist up until the time when the first skin clip is inserted to close the wound (at which point the anaesthetist will stop the sedation).

The alternative hypothesis is two-sided. The level of statistical significance is 5%. The clinical superiority of PMPS over ACPS will be shown if the mean rate is reduced by 29% (or more) when using PMPS, compared with ACPS. The randomisation schedule will be computer-generated using an 8-block design, with allocation advised by opaque sealed envelope. The expected recruitment rate into the study is 2 patients per week.

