## Background

The most commonly performed lower limb surgical arthroplasty procedures in the UK are primary hip replacement and primary knee replacement; respectively, 93,234 and 102,519 replacements were performed in 2016 (excluding Scotland) [1]. Regional anaesthesia, consisting of a spinal anaesthetic with or without peripheral nerve blockade, provides excellent operating conditions and post-operative analgesia, reduces the risk of venous thromboembolism, reduces transfusion requirements in the peri-operative period and avoids some of the risks associated with general anaesthesia [2].

Some patients are willing to experience surgery awake, but a significant proportion of patients are fearful of this experience pre-operatively and experience varying degrees of anxiety before and during the operation [3, 4]. Anaesthetists commonly supplement spinal anaesthesia with sedation medication delivered intravenously for lower limb arthroplasty in anxious patients. The aim of sedation is to reduce anxiety and promote psychological comfort, while minimising the physiological side effects induced by deeper planes of sedation.

Sedation for lower limb arthroplasty is often provided by the supervising anaesthetist using propofol by intravenous computer-assisted target-controlled infusion (anaesthetist-controlled propofol sedation (ACPS)) [5]. A target-controlled infusion (TCI) device delivers a variable rate of propofol in order to obtain and maintain a specified effect-site (i.e. brain) drug concentration, until such time as a new concentration is set by the supervising anaesthetist. Their use is standard anaesthesia practice in the UK.

There is, however, an unpredictable individual dose response to drugs inducing sedation, even using modern ACPS with TCI systems. Furthermore, anaesthetists have been shown to be poor judges of the pre-operative anxiety states of individual patients [6]. For a variety of reasons, including anxiety itself, patients do not always have preconceived expectations about how sedated they wish to be for surgery and these expectations are not always clearly communicated to (or understood by) the treating anaesthetist.

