For these reasons it is difficult for anaesthetists to sedate each individual to their preferred level using ACPS. Under-sedation results in an anxious patient because their anxiolytic requirements are unmet during surgery. Over-sedation results in a patient receiving an unnecessarily deep level of sedation and heightened exposure to the associated physiological harms even though the patient would have willingly experienced surgery at a lighter plane of sedation.

Patient-maintained propofol sedation (PMPS) involves the use of a TCI system delivering propofol where the effect-site concentration is influenced by the patient using a handheld trigger. Allowing patients to influence the depth of their sedation with a propofol TCI system has already been described in small case series in healthy volunteers [7] and in general [8], dental [9] and ambulatory outpatient surgery [10]. There are only three randomised controlled trials of PMPS and none of these use the Schnider effect-site-targeted propofol TCI model [5] to compare PMPS against ACPS [11–13]. Our aim is to assess the clinical efficacy of PMPS compared to ACPS. There is no commercially available device to perform PMPS, previous studies having relied on prototype devices. We have therefore designed and built a device capable of delivering PMPS for use in this clinical trial.

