### Study objectives

The primary research objective is to compare the body-weight-normalised rate of propofol consumption when sedation for surgery on adults undergoing elective primary lower-limb arthroplasty under spinal anaesthesia (effect-site-targeted with propofol) is patient-maintained versus when it is anaesthetist-controlled. The primary outcome will be expressed as milligrams propofol per kilogram actual body weight per hour of the sedation period. The sedation period is defined as the time from commencement of the allocated sedation regimen by the supervising clinical anaesthetist (which will be after spinal blockade is confirmed by clinical dermatomal testing) until the sedation regimen is discontinued at the end of surgery (which will be at the application by the operating surgeon of clips to skin).

The study primary null hypothesis is that there is no difference in the rate of propofol consumption when sedation it is patient-maintained versus anaesthetist-controlled. The primary alternative hypothesis is that a patient-maintained propofol sedation regimen will result in a minimum 29% reduction in the rate at which propofol is consumed over the course of the sedation period compared to anaesthetist-controlled propofol sedation.

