The secondary research objectives are:To establish whether patients are less deeply sedated intra-operatively during patient-maintained sedation compared to anaesthetist-controlled sedation.To assess whether patients undergoing PMPS have equal reductions in peri-operative anxiety compared to patients undergoing ACPS.To observe whether patients undergoing PMPS have comparable post-operative satisfaction with their sedation experience compared to patients undergoing ACPS.To explore whether patients who have undergone PMPS are fit for discharge from the post-anaesthetic care unit (PACU) sooner than patients who have undergone ACPS.To determine if patients undergoing PMPS have calculated effect-site concentrations of propofol that are lower than in patients who undergo ACPS.To examine how many times patients using PMPS press their trigger button to increment their dose (successful button press), how many times they press the button while the device is locked out (unsuccessful button press) and whether there is a relationship between pre-operative anxiety state and use of the trigger system.To determine whether patients undergoing PMPS experience a different incidence of airway, respiratory or cardiovascular sedation-related side-effects than patients who have undergone ACPS. Airway sedation-related side-effects include partial or complete airway obstruction that requires the usual clinical anaesthetist to apply one of the following interventions: chin-lift, jaw thrust, nasopharyngeal airway insertion, oropharyngeal airway insertion, laryngeal mask insertion or endotracheal tube insertion. Respiratory sedation-related side-effects are respiratory rate fewer than 8 breaths per minute or arterial oxygen saturations less than 88% in patients with chronic obstructive pulmonary disease (COPD) or 94% in all other patients. Cardiovascular sedation-related side-effects include heart rate or blood pressure reduction greater than 20% from baseline, but such events may be related to spinal anaesthesia rather than the sedation. All such events will be noted by a study investigator and reviewed to determine the likely aetiology. There are no objective clinical criteria to determine this, but routine clinical practice is to assimilate the presented information to estimate the likely contribution from sedation, spinal anaesthesia and/or another cause.To determine whether patients undergoing PMPS experience different health-related quality of life outcomes compared to patients undergoing ACPS.

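### The Statistical methods section lets a fall in propofol rate alone show clinical superiority, a rule that cannot separate a better-titrated regimen from one that under-sedates

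*Protocol article*

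**What the plan says.** **The decision rule.** Statistical methods: "The clinical superiority of PMPS over ACPS will be shown if the mean rate is reduced by 29% (or more) when using PMPS", relative to ACPS. The rate is defined under Study objectives: "The primary outcome will be expressed as milligrams propofol per kilogram actual body weight per hour of the sedation period". Nothing else enters the rule.

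**The purpose of sedation.** Background: "The aim of sedation is to reduce anxiety and promote psychological comfort, while minimising the physiological side effects induced by deeper planes of sedation". The same section describes failure in both directions. Over-sedation exposes the patient to avoidable physiological harm, and "Under-sedation results in an anxious patient because their anxiolytic requirements are unmet during surgery". It gives the trial's aim as assessing the clinical efficacy of PMPS against ACPS.

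**The scope of the claim elsewhere.** The Discussion part of the Abstract restricts the superiority question to propofol consumption. The hypotheses in the Abstract and under Study objectives are likewise stated only for the rate of consumption.

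**Anxiety and satisfaction.** Both are secondary. For anxiety: "To assess whether patients undergoing PMPS have equal reductions in peri-operative anxiety compared to patients undergoing ACPS". For satisfaction the objective is that the arms be comparable. No margin is given for either. The Statistical plan analyses secondary outcomes in complete cases free of major violations and mentions a Bonferroni correction.

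**The two regimens.** Under Trial intervention, PMPS begins at 0.5 μg/mL, which is also its floor. It rises by 0.2 per successful press to a ceiling of 2.0. After each successful press, "further button presses will not increase the target concentration for 2 min". Also, "If patients do not press the button for 15 min, the effect-site target will reduce by 0.1" μg/mL, repeating every 15 min down to the floor. In ACPS the anaesthetist raises and lowers the target at discretion: "No maximum or baseline levels will be pre-specified".

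**The concern.** Milligrams per kilogram per hour measures how much drug was given. By the article's own account, a good regimen gives enough to relieve anxiety and no more. Less drug is therefore an improvement only if anxiety relief is preserved, and the rule does not ask whether it was. Two quite different results would satisfy it equally: patients who chose lighter sedation and were comfortable, and patients who received too little and were anxious.

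The point matters more here because the arms differ by construction. PMPS starts at its lowest permitted target, is capped, is locked out between increments and drifts down without a press. ACPS has none of these fixed features. A lower rate in PMPS may partly reflect that structure as well as patient preference, and the primary outcome cannot distinguish the two.

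At stake is the headline. A report that follows the sentence literally could call PMPS clinically superior beside an anxiety comparison too imprecise to confirm or contradict it.

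**Working it through.** **1. The plan's own figures reproduce.** Inputs from Sample size calculation: PMPS 1.580 (SD 0.755), ACPS 2.231 (SD 0.915), 90% power, two-sided 5%, Welch's test.
- Difference: 2.231 − 1.580 = 0.651, and 0.651 / 2.231 = 29.2%. The 29% in the rule is the observed pilot difference.
- Power from the noncentral t distribution with Satterthwaite degrees of freedom: 35 per arm gives 89.2% and 36 per arm gives 90.07%, so 72 in total.
- Dropout: 72 / 0.9 = 80.

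The arithmetic is not at issue. It powers a test of consumption only.

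**2. The sections side by side.**

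| Place | What counts as success |
|---|---|
| Background | Anxiety relieved and comfort promoted with few side effects; too much and too little are both failures |
| Abstract, Discussion | Superiority on propofol consumption |
| Study objectives (hypotheses) | A lower consumption rate |
| Statistical methods | Clinical superiority, shown by a lower consumption rate |

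Only the last row moves from a consumption result to a clinical conclusion, and it does so without the other half of the aim in the first row.

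**3. Would the secondary outcomes catch under-sedation?** The article gives no SD or margin for anxiety, so effects are assumed in SD units, with 36 evaluable per arm and an unadjusted two-sided 5% level. Normal approximation: power = Φ(δ√(n/2) − 1.96), with √(36/2) = 4.243.
- δ = 0.3: Φ(1.273 − 1.96) = Φ(−0.687) ≈ 25%.
- δ = 0.5: Φ(2.121 − 1.96) = Φ(0.161) ≈ 56%.
- Half-width of the 95% interval: 1.96 × √(2/36) ≈ 0.46 SD.

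With 40 per arm the powers are about 27% and 61%. A Bonferroni correction lowers them further.

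For scale, a formal non-inferiority condition at one-sided 2.5% needs n per arm = 2(1.96 + z)² / margin², with z = 0.842 for 80% power and 1.282 for 90%. That is 63 (80%) or 85 (90%) for a margin of 0.5 SD, and 175 or 234 for 0.3 SD. The trial plans 36 evaluable per arm.

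**4. What the PMPS algorithm does to its own target.** Take a patient at a given target who never presses again, and compare the mean of max(start − 0.1 × floor(t/15), 0.5) with the same target held constant.

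| Start (μg/mL) | 60 min | 90 min | 120 min |
|---|---|---|---|
| 1.9 | 8% lower | 13% | 18% |
| 1.5 | 10% | 17% | 23% |
| 1.1 | 14% | 23% | 31% |

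Example from 1.5 over 60 min: (1.5 + 1.4 + 1.3 + 1.2) / 4 = 1.35, and 1 − 1.35/1.5 = 10%.

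This shows that automatic decay can be appreciable within the PMPS arm under an assumed pattern of no presses. It is not a comparison with ACPS, and the article gives neither durations nor press frequencies.

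**The case against.** **The sentence is bounded by the rest of the article.** The Abstract and the hypotheses speak only of consumption, and the Statistical plan tests mean rates at 5%. On this reading the Statistical methods sentence merely names the size of difference regarded as clinically relevant. That is a fair account of what the authors may have meant, and choosing consumption as primary with anxiety as secondary is a legitimate design preference. But the sentence as written states when clinical superiority has been shown, and the bounded wording elsewhere is a reason to bring it into line.

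**Patients can press for more.** This stands. Under Intervention they are given the trigger and told to press if they want deeper sedation. Each successful press of 0.2 offsets two decrements, and decay stops at 0.5. A lower rate may well be genuine preference. The rule simply cannot tell.

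**Much of the relevant reporting is already planned.** This also stands. Study objectives lists sedation depth, anxiety, satisfaction, effect-site concentrations and successful and unsuccessful presses. The Statistical plan models consumption alongside presses. No additional device-log table is requested.

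**A stronger reading to resist.** A reader might infer from the decay table that automatic decrements supply a third to all of the 29%, with no decision by the patient. The article does not support this. The 29% is PMPS against ACPS, whereas the table sets PMPS against itself held constant, and ACPS targets are also lowered at discretion. The table assumes 60 to 120 min without a press and an infusion rate proportional to target. From 1.9 over 60 min the fall is only 8%. Not pressing may also be a choice. Nor does the article show that PMPS does under-sedate.

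**Conclusion.** The point holds as a defect in the stated inference. The rule turns a consumption result into a clinical conclusion while ignoring anxiety relief, which the Background makes half of the aim. An under-sedating regimen could satisfy it.

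The consequence has no single number. What can be sized is the weakness of the safeguard: about 25% power to detect anxiety worse by 0.3 SD and 56% for 0.5 SD at 36 per arm. These rest on assumed effects, roughly normal scores and no multiplicity correction. The PMPS algorithm may contribute to a lower rate, but its share of the between-arm difference cannot be determined from the article.

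The primary endpoint, the test and the sample size of 72 inflated to 80 are not called into question here.

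**What to change.** Reword the Statistical methods sentence so that the primary result supports only lower body-weight-normalised propofol consumption with PMPS, consistent with the Abstract's Discussion and Study objectives. Drop clinical superiority as a conclusion drawn from consumption alone.

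Report the already planned between-arm anxiety and satisfaction comparisons beside the primary result, with confidence intervals. State that, at this sample size, an interval which fails to show harm is not evidence that the arms are equivalent. Making the claim conditional merely on intervals that do not show PMPS to be worse would not be an adequate substitute: without a margin, a truly worse regimen would often pass.

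Cost: a change of wording and a more modest headline claim. Treatment, sedation algorithms, primary endpoint and sample size are unchanged.

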### Sample size calculation

Our calculation is based on results from a pilot PMPS study (*n* = 26) and prospectively gathered standard care ACPS (*n* = 17), showing that the mean body-weight-normalised rate of propofol consumption in the PMPS and ACPS groups was 1.580 (SD = 0.755) and 2.231 (SD = 0.915), respectively. For power of 90% and level of significance of 5% against the two-sided alternative hypothesis, 72 participants are required to detect the observed difference in mean rate using Welch’s two-sample *t* test. Expecting 10% drop-out of participants, a sample size of 80 is required. Participants who drop out from the trial prior to randomisation will be removed from the study and any trial data that may have been collected on them or from them will be destroyed. All participants dropping out after randomisation will be included in the study by intention to treat and all trial data collected up to the moment of drop out will be retained for analysis.

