### Statistical plan

All data collected will be summarised for reporting purposes using descriptive statistics. The hypothesis test associated with the primary outcome will compare the two mean consumption rates using standard statistical tests chosen appropriate to underlying assumptions (e.g. two-sample *t* test and the Wilcoxon-Mann-Whitney test). Testing will be performed using datasets formed according to inclusions based on intention to treat. *P* values will be reported, with values less than 5% declared statistically significant.

We will report analyses of secondary outcomes for complete cases that contain no major clinical investigation plan violations. Amongst these, button-press data will be modelled using count data regression methods, with extension to bivariate models to distinguish between successful presses and unsuccessful presses. The panel time-series of propofol consumption rates collected throughout the sedation period alongside button presses will together be modelled using marked-point process methods. Ordinal responses recorded on a Likert scale (peri-operative anxiety, patient satisfaction) will be compared across trial arms using parametric methods suitable to underlying assumptions and non-parametric methods, such as the Wilcoxon rank sum test. Preoperative and post-operative quality of recovery total scores will be compared using the Wilcoxon matched pairs test. Inter-item correlations will be computed and associations between scored items will be compared using Spearman rank correlation. The Bonferroni correction to allow for multiple comparisons will be applied. Qualitative data obtained from structured questions will be coded and computer-analysed. Any missing outcome data will be imputed using either a last-observation-carried-forward rule or, for the subset of comparable secondary outcomes, use data routinely measured and recorded as part of usual clinical care.

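### The 29% threshold for clinical superiority is the planning effect itself, so the 90% power does not cover it (about 51% if applied to the point estimate)

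*Protocol article*

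**What the plan says.** All of the text is in the protocol article.

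- **Statistical methods** gives a rule for the clinical conclusion: "The clinical superiority of PMPS over ACPS will be shown if the mean rate is reduced by 29% (or more"). The same paragraph says "The alternative hypothesis is two-sided" and sets a 5% significance level.
- **Study objectives** has a null hypothesis of no difference, and an alternative that patient-maintained sedation "will result in a minimum 29% reduction in the rate at which propofol is consumed".
- **Sample size calculation** reports pilot and standard-care data in which the mean rate in the "PMPS and ACPS groups was 1.580 (SD = 0.755) and 2.231 (SD = 0.915), respectively". It then states: "For power of 90% and level of significance of 5% against the two-sided alternative hypothesis, 72 participants are required to detect the observed difference", using Welch's two-sample t test. Allowing 10% drop-out, 72 becomes 80.
- **Statistical plan** compares the two means by a standard test, with P "values less than 5% declared statistically significant".

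**The concern.** Two criteria bear on the primary outcome. One is a test of no difference at the 5% level, and this is what the trial was sized for. The other is a reduction of at least 29%, and no power is given for it. The 29% is not an independently chosen clinical margin. It is the pilot difference, which the sample size calculation also treats as the true effect. An estimate centred on its own threshold falls below it about half the time, however large the trial.

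At stake is what the trial may conclude. If patient-maintained sedation works just as planned, the trial is very likely to reject the null but has only about an even chance of meeting the 29% criterion. A significant reduction of, say, 22% could be presented as a success or as a failure, and the protocol does not settle in advance which of the two is the headline. That matters in an open-label superiority trial.

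**Working it through.** **Inputs** (Sample size calculation): PMPS mean 1.580, SD 0.755; ACPS mean 2.231, SD 0.915; two-sided 5%; 36 per arm (72) or 40 per arm (80). The threshold of 29% is from Statistical methods.

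**1. Source of the 29%.** (2.231 − 1.580)/2.231 = 0.651/2.231 = 29.2%.

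**2. Reproducing the stated sample size.** The standard error of the difference at 36 per arm is √((0.755² + 0.915²)/36) = √(1.40725/36) = 0.1977. The Satterthwaite degrees of freedom are 67.6, the critical t is 1.996 and the noncentrality is 0.651/0.1977 = 3.29. Noncentral-t power is 90.1% at 36 per arm (89.2% at 35). So 72 is right for the test named, and 72/0.9 = 80.

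**3. Smallest significant reduction.** 1.996 × 0.1977 = 0.395 mg/kg/h, and 0.395/2.231 = 17.7% of the ACPS mean. An observed reduction of 29% is therefore already significant at the planned variance, so the 29% criterion is the binding one.

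**4. Probability of meeting the 29% criterion at the planned effect.** The criterion is met when the observed PMPS mean is at most 0.71 times the observed ACPS mean. Let L = PMPS mean − 0.71 × ACPS mean.

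- Expected L = 1.580 − 0.71 × 2.231 = −0.004.
- SD of L at 36 per arm = √((0.755² + 0.71² × 0.915²)/36) = 0.166.
- P(L ≤ 0) = Φ(0.004/0.166) = 51.0%.
- At 40 per arm it is also 51.0%.
- If the true reduction is exactly 29%, it is 50% at any size.

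Simulation with normal and with gamma data gave 51%. Requiring P < 5% as well did not change the figure.

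**5. Significant but below 29%.** 90.1% − 51.0% = about 39% of trials, with observed reductions from about 18% to 29%.

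**6. True effect needed for 90% under the 29% criterion.** With SDs held at the pilot values, the true PMPS mean must be 0.71 × 2.231 − 1.2816 × 0.166 = 1.371. This is a true reduction of 1 − 1.371/2.231 = about 38.5% at 36 per arm.

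**7. Stricter reading.** If the 95% confidence interval had to exclude reductions below 29%, power would be Φ(0.004/0.166 − 1.96) = about 2.6%.

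| Criterion | Probability at the planned effect, 36 per arm |
|---|---|
| Two-sided Welch test, P < 5% | 90.1% |
| Observed reduction at least 29% | 51% |
| 95% interval excludes reductions below 29% | 2.6% |

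**The case against.** The best defence is that nothing in the calculation is wrong. The 90% is tied explicitly to Welch's test, it reproduces, and the protocol never claims it for the 29% criterion. A reader might infer that the stated power is false; the documents do not support that.

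A reader might also infer that the two rules are incompatible, or that a significant reduction between 18% and 29% has no defined result. Neither follows. The rules can be read as nested: the test governs statistical significance, and 29% governs a stricter clinical label. A result in that range is then significant with clinical superiority not shown. The stricter label cannot raise the type I error either. A directional expectation beside a two-sided test is common wording, and the test as specified is two-sided.

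Finally, the rule does not say that it applies to the observed means. It might be a loose statement of the target difference, in which case only the wording is at fault.

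These points stand and limit the concern, but they do not remove it. The sentence is phrased as a condition for showing superiority, and Study objectives repeats the figure as a minimum in the hypothesis. On the nested reading, the stricter label still has about 51% power, which is nowhere stated, and nothing says which label is the trial's main conclusion.

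**Conclusion.** The concern holds in a limited form. The sample size and its 90% power are correct for the two-sided test of no difference. The threshold for clinical superiority equals the assumed true effect, so that power does not extend to it: about 51% at 72 or 80 participants, with about 39% of trials significant but short of 29%. The protocol does not state which rule decides the superiority conclusion.

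These figures assume the pilot means and SDs, equal arms, and a rule applied to the point estimate. They barely depend on the distribution or the sample size. If the sentence was meant only to name the planning difference, the 90% is the relevant figure and the text needs rewording. This should be fixed, but it does not undermine the primary test, the significance level or the number of participants.

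**What to change.** In Statistical methods, state that superiority is concluded if the two-sided 5% test used for sizing (Welch) favours PMPS. Report the percentage reduction with its 95% confidence interval, and describe 29% as the planning difference. In Study objectives, write the alternative as the two mean rates being different.

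A sponsor may reasonably want to keep 29% as a benchmark of clinical relevance. If so, say that it is secondary to the test, that it applies to the observed means, and that its power is about 51% at the planned effect.

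Either way the change is to wording only and needs no extra participants. The cost is giving up 29% as a success threshold, or publishing its low power.
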